### Interim analyses {21b}

No interim efficacy analyses are planned. Recruitment feasibility will be monitored, and predefined stopping criteria apply solely for insufficient enrollment. Safety data will be reviewed periodically by the coordinating investigators. Only the principal investigators and the independent monitoring committee will have access to aggregated safety data, and they will make decisions regarding trial continuation or modifications if necessary.

### Methods for additional analyses (e.g., subgroup analyses) {20b}

Pre-specified subgroup analyses will explore whether the effect of targeted biopsy alone versus combined biopsy on the detection proportion of clinically significant prostate cancer (csPCa; ISUP ≥ 2) varies across clinically relevant strata, assessed at index biopsy.

Planned subgroup analyses include:PI-RADS category: PI-RADS 4 vs PI-RADS 5PSA density (PSAD): ≤ 0.15 vs > 0.15–0.20 vs > 0.20Biopsy approach: transrectal vs transperinealProstate volume: < 60 ml vs 60–100 ml vs > 100 mlAge categories: 50–60, 61–70, 71–75 yearsNumber of MRI lesions: single index lesion vs multiple lesionsMRI quality: PI-QUAL 2 vs PI-QUAL 3Follow-up imaging outcome: stable vs up- or downgraded PI-RADS at 12 monthsHistopathology outcome: ISUP 1 only vs no cancer on initial biopsy

Interaction terms will be evaluated using logistic regression models to assess effect modification on the primary endpoint. All subgroup analyses will be exploratory, hypothesis-generating, and interpreted descriptively without correction for multiplicity.

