#### Randomization scheme

Men with PI-RADS 4–5 or PI-RADS 3 with PSAD > 0.15 will be randomized 1:1 into Arm A (TB only) or Arm B (TB + SB).

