#### Secondary outcomes

Patient-reported outcomes (EPIC-26, EORTC-QLQ-C30, VAS)

Measured using validated questionnaires (metric: continuous scores), analyzed as mean changes over time and between groups (aggregation: mean differences), assessed at baseline, 30 days, and 12 months.Biopsy-related complications

Defined as adverse events within 30 days post-biopsy (measure: clinical assessment; metric: categorical/binary), summarized as proportions by study arm, assessed at 30 days post-procedure.Biopsy avoidance due to mpMRI triage

Defined as the proportion of participants not undergoing biopsy due to non-suspicious mpMRI findings (PI-RADS 1–2 or PI-RADS 3 with PSAD ≤ 0.15), reported as proportion, assessed at screening.Diagnostic performance of DRE

Defined as the association between DRE findings and biopsy outcomes (metric: sensitivity, specificity), analyzed cross-sectionally at baseline and biopsy.Biopsy approach (transrectal vs. transperineal)

Compared in terms of pain (VAS score) and infection rates (binary), summarized as mean differences and proportions, assessed within 30 days post-biopsy.MR in-bore biopsy yield

Defined as detection of csPCa in participants undergoing MR in-bore biopsy after negative or ISUP 1 results (metric: binary), reported as proportion, assessed within 3 months post-biopsy.Detection of higher-grade cancer (ISUP ≥ 3)

Defined as presence of ISUP ≥ 3 cancer on histopathology (metric: binary), reported as proportion, assessed at index biopsy.Comparison of bpMRI vs mpMRI

Retrospective comparison of detection performance (metric: paired binary outcomes), analyzed using constrained maximum likelihood methods, assessed at baseline imaging.Change in PI-RADS score

Defined as change in PI-RADS category between baseline and follow-up MRI (metric: ordinal change), reported as proportions of up- or downgrading, assessed at 12 months.Index-lesion-only analysis

Detection of csPCa based on index lesion targeting only (metric: binary), reported as proportion, assessed at index biopsy.AI and radiomics validation

Diagnostic performance of AI-based models (metric: AUC, sensitivity, specificity), analyzed retrospectively, assessed using baseline imaging and biopsy outcomes.

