### Participant timeline {13}

The participant timeline includes screening, enrollment, baseline assessments, randomization, biopsy procedures, and structured follow-up over 12 months. Only men with mpMRI findings of PI-RADS 4–5 or PI-RADS 3 with PSA density > 0.15 proceed to randomization. Follow-up includes standardized complication reporting, patient-reported outcome assessments, and repeat MRI depending on biopsy results (see Fig. 1).

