## Discussion

The PRIMA study is designed to resolve a central question in modern prostate diagnostics: is systematic biopsy still required for biopsy-naïve men in the era of high-quality mpMRI and fusion-guided TB? Current evidence remains mixed. Trials such as PRECISION [8], MRI-FIRST [9], and 4-M [10] confirmed that mpMRI-guided TB achieves high csPCa detection, but residual incremental detection from SB remains. Screening trials like STHLM3-MRI [11] and Göteborg-2 [12] further emphasized that omitting SB reduces overdetection but carries a marginal risk of missing csPCa. Thus, guidelines differ internationally, and a definitive, high-quality randomized trial within a controlled QA environment is urgently needed. Compared to prior studies, PRIMA features several distinguishing elements. First, strict preselection limits biopsy to men with PI-RADS 4/5 or PI-RADS 3 with PSAD > 0.15, consistent with German guideline recommendations [15, 24]. This enriched population minimizes unnecessary biopsies while maintaining csPCa yield. Second, mpMRI is mandatory rather than optional or replaced by bpMRI, ensuring maximal lesion characterization, especially in younger cohorts where imaging interpretation is more challenging [18, 19]. Third, uniform QA through PI-QUAL and operator certification standardizes both imaging and biopsy performance across all sites. Finally, inclusion of PROs allows holistic assessment of diagnostic burden, patient satisfaction, and complication profiles. The study also integrates advanced research objectives such as AI and radiomics model validation. By linking imaging features, histopathology, and PRO data, PRIMA aims to establish predictive algorithms for csPCa and quality-of-life outcomes, providing a platform for future personalized diagnostics. Expected benefits include reduced biopsy numbers, lower infection rates, and fewer ISUP 1 detections—leading to substantial health-economic savings [2, 3, 7]. Conversely, if SB omission compromises csPCa detection, results will clarify which subgroups (e.g., age, prostate volume, PI-RADS 3) still benefit from combined sampling. The standardized design and large sample will support guideline updates, reimbursement decisions, and possible nationwide implementation of MRI-only pathways if non-inferiority is demonstrated. Lastly, the PRIMA trial will further assess under which conditions and to what extent MRI in-bore biopsy constitutes a valid and safe approach within a targeted biopsy-only paradigm [25–28]. Limitations include potential selection bias toward academic centers with strong MRI expertise and limited generalizability to less-specialized institutions. Nevertheless, PRIMA’s rigorous QA, centralized monitoring, and defined endpoints ensure validity and reproducibility. Its findings will directly influence diagnostic policy, reduce overtreatment, and optimize early detection of clinically meaningful prostate cancer in Germany.

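### The lowest PSA-density subgroup cut equals the PI-RADS 3 entry cut and PI-RADS 3 has no subgroup level, so a PI-RADS 3 effect can surface only in part, under the PSA-density label

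*Protocol article*

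**What the plan says.** The Randomization scheme under Intervention description {11a} sets the entry rule: "Men with PI-RADS 4–5 or PI-RADS 3 with PSAD > 0.15 will be randomized 1:1". Participant timeline {13} confirms it: "Only men with mpMRI findings of PI-RADS 4–5 or PI-RADS 3 with PSA density > 0.15 proceed to randomization". The secondary outcome on biopsy avoidance places the remaining PI-RADS 3 men among those not biopsied, because of "non-suspicious mpMRI findings (PI-RADS 1–2 or PI-RADS 3 with PSAD ≤ 0.15").

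The subgroup section {20b} then lists its factors, run together in the extracted text: "Planned subgroup analyses include:PI-RADS category: PI-RADS 4 vs PI-RADS 5PSA density (PSAD"). The PSAD strata are up to 0.15, above 0.15 to 0.20, and above 0.20. On method it says "Interaction terms will be evaluated using logistic regression models to assess effect modification on the primary endpoint", and on status "All subgroup analyses will be exploratory, hypothesis-generating, and interpreted descriptively without correction for multiplicity".

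The Discussion says that, if leaving out systematic biopsy (SB) compromises detection of clinically significant cancer, "results will clarify which subgroups (e.g., age, prostate volume, PI-RADS 3) still benefit from combined sampling".

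**The concern.** The same value, 0.15, serves as the entry threshold for PI-RADS 3 and as the lowest boundary of the PSAD subgroup. The contrast between the lowest PSAD stratum and the higher ones is therefore also, in part, a contrast between men without and men with PI-RADS 3. PSAD and MRI category are entangled by the entry rule, not by chance.

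The PI-RADS factor does not help to separate them. It has two levels, 4 and 5, and PI-RADS 3 belongs to neither. Among the listed factors, PSAD is the only one whose strata divide PI-RADS 3 from the rest by rule. If SB adds more (or less) in PI-RADS 3 men, the listed subgroups cannot show this directly, and part of it can show up under PSAD.

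At stake is the reading of the subgroup results. The Discussion names PI-RADS 3 as a group on which the trial will inform, and PSAD is the trial's own triage variable.

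**Working it through.** **Inputs from Sample size {14}.** There are 477 analyzable men per arm, so 954 randomized. Expected shares of all men are 10% PI-RADS 3 with PSAD above 0.15, 30% PI-RADS 4 and 20% PI-RADS 5, so 60% are randomized. The control detection rate is 50%, the assumed true difference −5 points, and the margin 13 points, with one-sided alpha 0.05 and 80% power.

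**The plan's own figure.** A simple unpooled formula gives (1.645 + 0.842)² × (0.25 + 0.2475) / 0.08² = 481 per arm. The score version, with the null variance restricted to the margin, gives 476.02, rounded up to 477. The stated number reproduces, and 2 × 477 / 0.6 = 1590. The base of 954 is sound.

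**Expected composition of the randomized men.**
- PI-RADS 3: 954 × 10/60 = 159
- PI-RADS 4: 954 × 30/60 = 477
- PI-RADS 5: 954 × 20/60 = 318, so PI-RADS 4–5 together is 795

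**PI-RADS 3 share of each PSAD stratum.** At PSAD up to 0.15 it is zero by the entry rule, apart from men randomized in error and kept under intention to treat. Above 0.15 it is 159 / (159 + 795q), where q is the fraction of PI-RADS 4–5 men with PSAD above 0.15. The article does not give q, so I vary it. Even at q = 1 the share is 159/954 = 16.7%.

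**Carry-over.** With no true PSAD effect, and on the risk-difference scale, the apparent gap between the strata above 0.15 and the stratum below is the PI-RADS 3 share times (loss in PI-RADS 3 minus loss in PI-RADS 4–5). The losses below are assumed, in percentage points. Each pair keeps the protocol's overall 5 points, because (1/6) × PI-RADS 3 loss + (5/6) × PI-RADS 4–5 loss = 5.

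| q | PI-RADS 3 share above 0.15 | Gap, losses 10 and 4 | Gap, losses 15 and 3 | Gap, losses 20 and 2 |
|---|---|---|---|---|
| 0.3 | 40% | 2.4 | 4.8 | 7.2 |
| 0.5 | 29% | 1.7 | 3.4 | 5.1 |
| 0.8 | 20% | 1.2 | 2.4 | 3.6 |

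**Comparison with sampling error.** With rates near 50% and 45%, the standard error of the difference in arm effect between men above and below 0.15 is √(0.995/n_high + 0.995/n_low), where 0.995 = 2 × 0.4975.
- q = 0.3 (398 high, 556 low): 6.6 points
- q = 0.5 (556 high, 398 low): 6.6 points
- q = 0.8 (795 high, 159 low): 8.7 points

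The spurious gap alone would reach two-sided p < 0.05 in about 5–7% of trials for losses of 10 and 4, 6–11% for 15 and 3, and 7–20% for 20 and 2, against 5% by chance.

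**PI-RADS 3 in the listed subgroups.** The PI-RADS factor covers 477 + 318 = 795 men and omits the 159. No other listed factor isolates them, so the list does not match the Discussion's statement about PI-RADS 3.

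**The case against.** The strongest reply is that little depends on this. The subgroup analyses are declared exploratory and descriptive, and the primary test, alpha and sample size are untouched. If the effect of omitting SB is the same in PI-RADS 3 as in PI-RADS 4–5, the bias is zero. If it differs, the carry-over in most of the scenarios is well under one standard error. The illustration is also on the risk-difference scale, while the plan is for logistic interactions. Finally, the stratum estimates remain correct as descriptions: in this pathway a biopsied man with PSAD up to 0.15 is PI-RADS 4–5 by definition. All of this stands, and it is why the point is minor. It does not remove the built-in overlap, nor does it give PI-RADS 3 a place in the list.

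Four stronger readings are tempting and are not supported:
- A reader might infer that the models leave PI-RADS unadjusted. The section names interaction terms and does not say which other terms enter. The analysis plan, still to be finalized under {20a}, may add them. The defect lies in the subgroup definitions stated here.
- A reader might infer that a PI-RADS 3 effect is bound to be taken for a PSAD effect. It can be, in part, and only if the effects differ.
- A reader might extend the point to prostate volume, since a larger gland needs a higher PSA to exceed 0.15. No volume band excludes PI-RADS 3, and the article gives no PSA or volume distribution with which to size any imbalance.
- A reader might extend it to the contrast between the two upper PSAD strata. PI-RADS 3 men can be in both, so the entry rule forces nothing there.

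**Conclusion.** The point holds as a minor one. That the lowest PSAD stratum contains no eligible PI-RADS 3 man, and that all of them (expected 159 of 954) lie above it, follows exactly from the entry rule and the subgroup cut. So does the absence of a PI-RADS 3 level, which conflicts with what the Discussion expects the results to show.

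The size is conditional. About 20–40% of any difference in effect between PI-RADS 3 and PI-RADS 4–5 would carry into the PSAD contrast. This assumes that 80–30% of PI-RADS 4–5 men have PSAD above 0.15 and that PSAD itself has no effect. In the scenarios shown that is 1.2 to 7.2 points, against a standard error of about 6.6 to 8.7. Only exploratory analyses are concerned.

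**What to change.** In the subgroup section {20b}:
- Make the PI-RADS factor three levels: 3 (randomized only with PSAD above 0.15), 4 and 5.
- Estimate effect modification by PSAD within PI-RADS 4–5, about 795 men, or in a model that also contains PI-RADS category and its interaction with arm.

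Carry the same definitions into the analysis plan. No data collection changes, and no participant had been enrolled at submission.

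Restriction removes 159/954, about one sixth, of the men from the PSAD test. With the same variance formula at q = 0.5, the standard error goes from 6.6 to √(0.995 × 2/397.5) = 7.1 points. The new PI-RADS 3 row has about 80 men per arm, so its arm difference would have a standard error of about √(0.4975/79.5) = 7.9 points if rates are near 50% and 45%. It should be presented as an imprecise estimate, not as a test.

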### Strategies to improve adherence to interventions {11c}

As PRIMA is a diagnostic accuracy trial without therapeutic intervention, adherence is expected to be high. All participants (Arms A and B) benefit from access to high-quality mpMRI and standardized biopsy procedures at experienced centers, which is commonly perceived as advantageous care. All participants receive structured follow-up imaging and, if indicated, MR in-bore biopsy to ensure that csPCa is not missed in either study arm, reducing concerns about randomization.

Adherence will be supported through clear communication, appointment reminders, and direct contact with study nurses. Completion of scheduled procedures will be monitored through the electronic trial database, and adherence metrics will be reviewed in monthly Trial Steering Committee meetings.

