### Outcomes {12}

#### Co-primary outcomes

Detection of clinically significant prostate cancer (csPCa; ISUP ≥ 2)

Defined as the presence of csPCa on histopathology at initial biopsy (measure: histopathological assessment; metric: binary yes/no). Results will be expressed as the proportion of participants with csPCa in each study arm (method of aggregation: proportion), assessed at index biopsy (timepoint).Detection of clinically insignificant prostate cancer (ISUP 1)

Defined as the presence of ISUP grade group 1 cancer on histopathology at initial biopsy (measure: histopathological assessment; metric: binary yes/no). Results will be expressed as the proportion of participants with ISUP 1 cancer in each study arm, assessed at index biopsy.

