### Plans to promote participant retention and complete follow-up {18b}

Participant retention in PRIMA is supported by clear communication of the clinical relevance of structured imaging follow-up and by scheduling support from study nurses at each site. Reminder systems, including scheduled telephone, electronic or postal notifications, will be used to encourage attendance at follow-up visits, particularly the 30-day safety visit and the 12-month mpMRI assessment. Missed appointments will be actively followed up by site investigators or study nurses to re-schedule assessments where feasible.

If participants discontinue allocated biopsy procedures, routinely collected clinical data—including follow-up MRI results, histopathology reports, adverse events and patient-reported outcomes—will continue to be collected unless consent is formally withdrawn. Reasons for withdrawal or protocol deviation will be documented in the electronic trial database.

For participants lost to follow-up, electronic hospital records may be reviewed to identify biopsy results, MRI findings, or cancer diagnoses when permitted by local data-protection regulations. Participants diagnosed with csPCa (ISUP ≥ 2) will exit the trial and enter guideline-based standard-of-care treatment; data collection until the time of exit remains part of the primary analysis.

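### The histopathology subgroup for index-biopsy csPCa has no events by definition, the 12-month PI-RADS subgroup is measured after that outcome, and the PI-RADS contrast leaves out PI-RADS 3

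*Protocol article*

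**What the plan says.** The protocol's section on additional analyses {20b} gives one outcome for the whole list of subgroups: whether the effect of biopsy arm on csPCa detection "varies across clinically relevant strata, assessed at index biopsy". Effect modification is to be judged by interaction terms in logistic regression on the primary endpoint. The Outcomes section {12} fixes that endpoint: "Defined as the presence of csPCa on histopathology at initial biopsy".

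Three entries on the list matter here:

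- Histopathology outcome: "ISUP 1 only vs no cancer on initial biopsy".
- Follow-up imaging outcome: PI-RADS unchanged at 12 months, or moved up or down.
- PI-RADS category: 4 against 5, with no level for PI-RADS 3.

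On who has a 12-month MRI, the retention section {18b} says: "Participants diagnosed with csPCa (ISUP ≥ 2) will exit the trial and enter guideline-based standard-of-care treatment". The participant timeline {13} provides for "repeat MRI depending on biopsy results". The adherence section {11c} reads differently: "All participants receive structured follow-up imaging and, if indicated, MR in-bore biopsy".

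Men with PI-RADS 3 and PSAD > 0.15 are randomized (randomization scheme in {11a}). The Discussion says that, if omitting SB compromises csPCa detection, "results will clarify which subgroups (e.g., age, prostate volume, PI-RADS 3) still benefit from combined sampling".

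**The concern.** A subgroup analysis asks whether the arm effect on an outcome differs between groups of men defined independently of that outcome. Two entries on the list do not meet this requirement. The histopathology entry is built from the result of the biopsy that also defines the outcome. The 12-month imaging entry is observed a year later, in men whose presence at that visit depends on the outcome. The first analysis cannot be carried out. The second, where it can be carried out, cannot be read as effect modification.

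The PI-RADS entry has a different fault. It leaves out one of the three randomized imaging categories, and that category is one the Discussion gives as an example. If the list is carried into the SAP unchanged, the analyst must either report an inestimable model or change a pre-specified analysis after the fact.

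**Working it through.** **1. The plan's own figure, used for the counts below.** Inputs from Sample size {14}: csPCa 50% with TB + SB, 45% with TB alone, margin 13 points, one-sided α = 0.05, power 80%. The distance to the margin is 0.13 − 0.05 = 0.08. With score-type variance the null-restricted rates are 0.4105 and 0.5405.

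- Null SD term: √(0.4105 × 0.5895 + 0.5405 × 0.4595) = 0.700
- Alternative SD term: √(0.45 × 0.55 + 0.50 × 0.50) = 0.705
- n = [(1.645 × 0.700 + 0.842 × 0.705) / 0.08]² = 476.02 before rounding of the inputs, that is 477 per arm

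The stated 477 is reproduced, with power 0.801. The point disputes no figure in the plan.

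**2. Histopathology subgroup.** Under the plan's rates, ISUP 1 is 15% in Arm B and 0.60 × 15% = 9% in Arm A. No cancer is then 1 − 0.50 − 0.15 = 35% in Arm B and 1 − 0.45 − 0.09 = 46% in Arm A.

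| Index-biopsy result | Arm A (of 477) | Arm B (of 477) | csPCa events in the row |
|---|---|---|---|
| csPCa (ISUP ≥ 2) | 214.65 | 238.5 | all, 453.15 |
| ISUP 1 only | 42.93 | 71.55 | 0 |
| No cancer | 219.42 | 166.95 | 0 |

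In both levels and both arms the detection proportion is 0. The risk difference is 0 − 0 and the odds ratio is 0/0. A logistic model restricted to these men has a constant outcome and no finite maximum-likelihood estimate; fitted to a data set simulated under these rates, it stops with a singular matrix. Keeping the men with csPCa as a third level does not help, because the outcome is then always 1 in that level and the factor predicts it perfectly. csPCa found later by in-bore biopsy does not count, because the stated timepoint is the index biopsy.

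The strata are also shaped by arm. Among men without csPCa, ISUP 1 makes up 42.93 / (42.93 + 219.42) = 16.4% in Arm A and 71.55 / (71.55 + 166.95) = 30.0% in Arm B. Any comparison of arms within a stratum is therefore not a randomized one.

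**3. Follow-up imaging subgroup.** No arithmetic is needed; the question is which men have a 12-month MRI.

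- Under {18b} and {13}, men with csPCa exit and repeat MRI depends on the biopsy result. The strata then consist of men without observed index csPCa, and the situation is that of step 2.
- Under the wording of {11c}, some men with index csPCa could have a 12-month MRI. Events would exist, but the stratifying variable would still be recorded after the outcome and after the care that followed from it.

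**4. PI-RADS contrast.** From the expected distribution in {14}, the randomized categories are 10% (PI-RADS 3 with PSAD > 0.15), 30% (PI-RADS 4) and 20% (PI-RADS 5).

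- PI-RADS 3: 10/60 = 16.7%; 954 × 10/60 = 159 men, 79.5 per arm
- PI-RADS 4: 477 × 30/60 = 238.5 per arm
- PI-RADS 5: 477 × 20/60 = 159 per arm

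The base of 954 is 2 × 477 analyzable men. With the dropout allowance it is 0.6 × 1908 ≈ 1145, of whom 10/60 is about 191.

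The PSAD subgroup is no substitute, since PSAD > 0.15 mixes PI-RADS 3, 4 and 5.

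**5. Precision of an added PI-RADS 3 level.** The plan gives no csPCa rate for this level. The widest 95% half-width, with 50% in both arms, is 1.96 × √(0.50 / 79.5) = 15.5 points. With an assumed 20% in both arms it is 1.96 × √(0.32 / 79.5) = 12.4 points.

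**The case against.** The strongest defence is that little depends on this list. Section {20b} calls all subgroup analyses exploratory and descriptive, and no error rate, endpoint or sample size rests on them. The two post-outcome entries also resemble secondary outcomes that the plan already has: in-bore yield after a negative or ISUP 1 result, and change in PI-RADS at 12 months. They may simply be listed under the wrong outcome. All of this stands, and it limits the severity. It does not make the histopathology interaction estimable.

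Three stronger readings are tempting and should not be adopted.

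- A reader might infer that the 12-month subgroup, like the histopathology one, cannot contain a single csPCa event. That does not follow from a definition. It rests on the exit rule, against which {11c} speaks of imaging for all participants. In addition, men who do not complete the allocated biopsy may stay in follow-up ({11b}, {18b}), and their missing index outcome may be imputed as csPCa ({20c}). What can be said is no or almost no observed events.
- A reader might infer that PI-RADS 3 will have no result at all. The list is introduced as a set of included examples, the SAP is not shown, and the Discussion sentence is conditional and illustrative. These men also stay in the primary analysis and in the other baseline subgroups. The point is an inconsistency in one contrast.
- A reader might infer that PI-RADS 3 is where the need for SB is most uncertain. The protocol does not rank it so; the Discussion names it beside age and prostate volume.

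**Conclusion.** The point holds in three parts of unequal strength.

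- **Histopathology subgroup:** zero csPCa events in all four cells, by definition and whatever the true rates. The stated interaction cannot be estimated. This part rests on {12} and {20b} alone and needs no assumption.
- **12-month PI-RADS subgroup:** not a valid effect modifier for an index-biopsy outcome, whichever imaging wording applies. That it has no or almost no observed events depends on the exit rule being applied as written.
- **PI-RADS 3:** a mismatch between the 4-against-5 contrast and both the randomized population and the Discussion. It concerns about one man in six (159 of 954, about 80 per arm), if the planned distribution is right.

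The list should be corrected, but nothing here bears on the trial's main conclusion.

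**What to change.** - Remove the histopathology and 12-month imaging entries from the list of interaction tests on index csPCa. Alternatively, keep them as descriptive tables by arm for csPCa found after the index biopsy (in-bore or follow-up), tied to the existing secondary outcomes on in-bore yield and PI-RADS change. State that these strata arise after randomization, so that differences between arms within them are not randomized comparisons.
- Define the PI-RADS subgroup as 3 (with PSAD > 0.15) vs 4 vs 5, and say beforehand that the PI-RADS 3 level will be imprecise.
- Reconcile the statements on follow-up imaging in {11c}, {13} and {18b}, so that it is clear which men have a 12-month MRI.

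The cost is protocol and SAP wording only. No new data are needed, the SAP is still to be finalized, and no participant had been enrolled when the article was submitted.
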